## Abstract

**Introduction:**

The UK has worse cancer outcomes than most comparable countries, with a large contribution attributed to diagnostic delay. Electronic risk assessment tools (eRATs) have been developed to identify primary care patients with a ≥2% risk of cancer using features recorded in the electronic record.

**Methods and analysis:**

This is a pragmatic cluster randomised controlled trial in English primary care. Individual general practices will be randomised in a 1:1 ratio to intervention (provision of eRATs for six common cancer sites) or to usual care. The primary outcome is cancer stage at diagnosis, dichotomised to stage 1 or 2 (early) or stage 3 or 4 (advanced) for these six cancers, assessed from National Cancer Registry data. Secondary outcomes include stage at diagnosis for a further six cancers without eRATs, use of urgent referral cancer pathways, total practice cancer diagnoses, routes to cancer diagnosis and 30-day and 1-year cancer survival. Economic and process evaluations will be performed along with service delivery modelling. The primary analysis explores the proportion of patients with early-stage cancer at diagnosis. The sample size calculation used an OR of 0.8 for a cancer being diagnosed at an advanced stage in the intervention arm compared with the control arm, equating to an absolute reduction of 4.8% as an incidence-weighted figure across the six cancers. This requires 530 practices overall, with the intervention active from April 2022 for 2 years.

**Ethics and dissemination:**

The trial has approval from London City and East Research Ethics Committee, reference number 19/LO/0615; protocol version 5.0, 9 May 2022. It is sponsored by the University of Exeter. Dissemination will be by journal publication, conferences, use of appropriate social media and direct sharing with cancer policymakers.

**Trial registration number:**

ISRCTN22560297.

STRENGTHS AND LIMITATIONS OF THIS STUDYImprovements in primary care are seen as a key for improving early cancer diagnosis in the UK, and this trial is targeting that part of the diagnostic pathway.This is a large, definitive trial, powered to identify a clinically important difference in cancer stage at diagnosis.The trial is designed to minimise impact on participating practices, with outcome data being obtained from routinely collected National Health Service data.One limitation is that the UK’s national imperative to improve cancer diagnosis after the COVID pandemic may mean that use of other interventions (or eRATs themselves) is encouraged by policymakers, reducing the validity and reliability of the trial.

## Introduction

An estimated 10 000 UK cancer deaths each year would not occur if the UK matched the outcomes of other European countries.^1^ Much of the difference is attributed to diagnostic delay.^2^ The National Health Service (NHS) long-term plan, published in January 2019, specifically targets an increase in the percentage of patients with cancer whose cancer is stage 1 or 2 (thus potentially curable) at diagnosis to rise from the current 54% to 75% by 2028.^3^ Diagnosis of cancer may occur by several routes, but the main ones are population screening, and diagnosis after symptoms have occurred. Although screening for cancer is effective for colorectal, breast, lung and cervical cancers,^4–6^ less than 10% of total new UK cancers are identified by this route. Most of the remainder are diagnosed after presenting with symptoms, usually to primary care. Of patients with cancer, just under 20% present with an emergency complication of their cancer; however, many of these patients have previously reported symptoms attributable to their cancer to primary care, but this presentation did not lead to a diagnosis of cancer.^7^

Within general practice, many studies have aimed at identifying the symptoms of possible cancer and quantifying their predictive value.^8^ One main output has been risk assessment tools (generally abbreviated to RATs); these give precise estimates of the chance of an underlying cancer as a percentage figure. RATs provide precise estimates for single symptoms (eg, the risk of cancer of the lung for a person aged 40 years or more with haemoptysis is 2.4%), as pairs of symptoms (haemoptysis accompanied by loss of weight is 9.2%) or as repeated symptoms (a re-attendance with haemoptysis is 17%).^9^ RATs are published for the 18 most common adult cancers, accounting for nearly 90% of the total cancer burden. These publications have been highly influential: in particular, they strongly contributed to the National Institute for Health and Care Excellence (NICE) guideline, ‘Suspected cancer: recognition and referral (NG12)’, which guides symptomatic diagnosis of cancer in the UK.^10^

The initial RATs, of paper, mouse mat, calendar, or web-based forms, increased cancer diagnostic activity,^11^ although their impact on hard outcomes, such as stage at diagnosis or cancer survival, were unknown. Electronic RATs (eRATs) for seven major cancers (lung, colorectal, pancreas, oesophago-gastric, bladder, kidney and ovary) have been developed for the two largest UK primary care electronic healthcare record systems, SystmOne and EMIS, used in around 80% of English practices. The software performs daily calculations of individual cancer risk in patients aged 40 and over, using coded symptoms and laboratory results in the patient’s record over the past year, and prompts the general practitioner (GP) when the risk of one or more of these cancers is equal to or above 2%. Some form of electronic clinical decision support for cancer diagnosis has been downloaded by practices and used by at least one practice member in approximately 12% of English practices.^12^ Two systematic reviews recently concluded that more research evidence was needed for impact on time to diagnosis and treatment, stage at diagnosis and health outcomes, as well as research to understand how tools are used in GP consultations.^13^ A feasibility trial of the oesophago-gastric eRAT published after these systematic reviews reported installation and regulatory problems that severely restricted use,^14^ and a vignette study of the colorectal RAT suggested it changed the GP’s inclination to refer in 26% of uses.^15^

One crucial aspect of eRAT research relates to cost-effectiveness: annual NHS spending on cancer diagnosis is approximately £1bn.^16^ Observational data showed that increased use of the urgent cancer referral system improved survival,^17^ but there are insufficient data to inform a cost-effectiveness analysis of the subject.^13^

### Objectives

The overarching aim of the trial is to assess the clinical and cost-effectiveness of using eRATs for six cancer sites—colorectal, lung, bladder, kidney, oesophago-gastric and ovarian cancers—compared with usual care for patients in general practice. Our hypothesis is that provision of eRATs will expedite the diagnosis of symptomatic cancer resulting in better cancer outcomes.

The primary objective is to compare the effects of using eRATs (vs usual care) on the percentage of patients with a newly diagnosed cancer at one of the six sites whose cancer is staged as being stage 1 or 2 (vs stage 3 or 4).

A secondary objective is to investigate differences in the stage at diagnosis of a further six cancers without eRATs (combined): breast, melanoma, prostate, non-Hodgkin's lymphoma, larynx and uterus. This is to investigate the possibility of an effect whereby eRATs are associated with increased diagnostic activity beyond the eRAT cancers. We will also investigate differences in the number of patients diagnosed with the six eRAT cancers combined, and the total number of cancers (excluding non-melanoma skin cancer) diagnosed, use of the 2-week wait referral system (the main pathway for urgent investigation of possible cancer in England) or equivalent for the six eRAT cancers combined, and across all cancers; the routes to diagnosis for each of the six eRAT cancers,^18^ and for the six comparator non-eRAT cancers; the proportion of patients on a 2-week wait pathway receiving a diagnosis of cancer; whether a patient on a 2-week wait pathway has a diagnosis of cancer established (or refuted) within 28 days; 30-day and 1-year survival for those with cancer; the rate of cancer investigations—namely colonoscopies, sigmoidoscopies, upper gastro-intestinal endoscopies, chest X-ray examinations, abdominal ultrasound scans and abdominal CT scans. We will also conduct parallel cost-effectiveness analyses, service delivery modelling and a process evaluation.

## Methods and analysis

### Design and setting

The study is a pragmatic cluster randomised-controlled trial in England, in primary care medical practices using one of the two (SystmOne or EMIS) electronic record keeping systems. The clusters are practices, a term which includes single practices, and small groups of practices agglomerated administratively to single entities. These will be randomised 1:1 to receive either the intervention (access to the suite of eRATs) or usual care. Online supplemental appendix A shows pathways to a cancer diagnosis in the UK and illustrates how the intervention is expected to have an effect. It is unrealistic to offer eRATs to individual GPs, as there would be considerable contamination within any practice. Nevertheless, for a practice to be eligible to take part, we ask at least 50% of GPs in that practice to agree to use the eRATs. Although the intervention is at the practice level, some process and resource use measures and all main trial primary and secondary outcomes relate to individual patients.

10.1136/bmjopen-2022-065232.supp1Supplementary data

### Intervention

#### The eRATS

The eRATs have been developed by a specialist IT team, Informatica systems Ltd, in partnership with the cancer charity, Macmillan. The risk estimates in the eRATs are from the original research papers for each cancer site.^9 19–24^ Practices will access the software via a new cloud-based system called Skyline, specifically designed to facilitate efficient integration into GP clinical systems. CA marking of the Skyline version of eRATs was obtained in September 2021.

The eRATs have multiple functions. The first is the *‘prompt’*. This collates relevant coded symptoms and blood tests in the patient’s medical record from the previous 12 months, which are then assessed for the possibility of cancer, generating a risk score equivalent to the positive predictive value of the cancer features for each cancer. A prompt (pop-up), displaying the risk score(s), appears on screen when a registered user opens a patient’s medical records and indicates that patient has a risk of 2% or higher for at least one of the studied cancers.

A second function is the *‘symptom checker’*, allowing the clinician to add additional patient’s symptoms to the eRAT checklist on screen; this process automatically recalculates the risk of any of the six cancers. On reviewing the risk score from the prompt and/or symptom checker, the clinician then decides the best course of management, which may be: (i) clinical review in primary care; (ii) ordering of test/investigations or (iii) referral to secondary care. Embedded within all eRATS are links to authoritative guidance regarding the early diagnosis of cancer, NICE NG12,^10^ Macmillan’s abbreviated NICE guidance,^25^ and Cancer Research UK guidance.^26^ These sources of information are added to assist management of the patient, but the decision whether or not to investigate is for the clinician and patient. Some EMIS practices also have access to the QCancer risk tool,^27^ although embedded in a dormant state within the practice IT and record system, and requiring manual activation before operation. All practices will be asked not to use it during the trial.

#### Justification of cancer sites

RATs are available for 18 adult cancers, each varying in their incidence, ease of diagnosis, amenability to treatment and proportion presenting as an emergency.

We elected to study cancer sites (a) which were in the top 15 cancers by incidence; (b) for which curative treatment is reasonably possible in symptomatic patients^28^ and (c) with a significant percentage of patients presenting as an emergency.^29^ Using these criteria, six cancer sites were selected, amounting to approximately half of all incident cancers. The selected six were: lung, colorectal, oesophago-gastric, ovary, kidney and bladder. The remaining nine cancers were considered as comparators to examine any practice level effect of increased cancer diagnostic activity. Three of these nine cancers, brain, pancreas and leukaemia, were removed for clinical and practical reasons: no eRAT is available for brain or leukaemia; in both brain and pancreas, symptomatic diagnosis is considered to have a very small likelihood of improving survival,^28^ and in leukaemia, a full blood count (easily available in primary care) will usually establish the diagnosis, making an eRAT unlikely to expedite the diagnosis.^30^

### Training practices in using eRATS

Training in the use of the eRATs uses short, prerecorded videos available online coordinated by a practice ‘research champion’. These videos show GPs how to use the prompt and symptom checker functions.

### Duration of intervention

Practice recruitment started in August 2019 and is expected to finish at the end of March 2022, including installation of the eRATs software. The trial was paused for 6 months in March 2020 owing to COVID-19. The formal start of the intervention window will be 1 April 2022 (although some practices might have delayed installation) and will close for all intervention practices on 31 March 2024.

### Usual care

Patients presenting to the control practices will experience the GP’s usual diagnostic approach. GPs in control practices will have no specific on-screen prompt, although they may have access to hard copy (eg, paper or mouse mat) versions of the RATs, or to other cancer tools such as those supporting structured follow-up of symptomatic patients not selected for initial investigation. For EMIS practices with QCancer dormant in the system, control practices are expected to leave it dormant. We will document control practice use of RATs, other decision support tools, and access to and use of eRATs via interim and exit questionnaires completed within the first 12 months of a practice commencing the intervention and at the end of the trial. In line with intervention practices, trial time will formally begin for control practices on 1 April 2022 and end on 31 March 2024.

### Data collection window

Outcome data for all practices will be obtained for the 2-year period from 1 June 2022 to 29 May 2024. This data collection window is lagged behind the trial time window (1 April 2022 to 31 March 2024) in order to: (a) provide some time for practices to become accustomed to how the intervention functions prior to data collection and (b) to have a 2-month window following the end of the intervention window in order to allow cancers to be diagnosed in patients seen towards the end of that window.

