For rate outcomes (number of 2-week wait referrals, cancers and imaging investigations), we will analyse the rates per 100 000 registered patients per year by age–sex strata using mixed-effects Poisson regression models including a random intercept for practice. These models will include trial arm as a predictor and will adjust for the age and sex of the strata, and at the practice level for the minimisation variable (2-week wait referral ratio) and deprivation (quintile of IMD overall score). The models will be further adjusted at the practice level for list size, clinical IT system used, Care Quality Commission overall rating, and for the age and sex case mix of practices should these covariates be found to be associated with the outcome (even if not unbalanced with respect to allocation). Case mix will be incorporated by including variables for counts of practice populations in different age–sex strata (5-year age groups by sex, excluding one age–sex stratum that can be determined once all others are known).

All the above analyses will combine data for the six eRAT cancers for each model. For outcomes related to 2-week wait referrals, data will be combined for all referral pathways relevant to the six eRAT cancers. To investigate whether the eRATs produce a spillover effect, whereby diagnostic activity is increased for other cancers, we will repeat all analyses using data for the six non-eRAT cancers combined for each model. Investigation of a spillover effect for 2-week wait referral outcomes will use data for all referral pathways combined.

Additional sensitivity analyses will be conducted for the primary outcome in order to explore moderation arising from practice-level characteristics, using interaction terms. Although the trial has not been powered to detect low-to-moderate subgroup differences, such as differences in a single cancer site, large interaction effects that differ with respect to the direction of effect across subgroups are of interest. The potential impact of missing staging data on the primary outcome will also be explored through use of multiple imputation methods making use of auxiliary variables, such as survival time, morphology and grade, to improve the missing at random assumption in line with previous work).^37^

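### Referral and investigation rates are counted for up to 59 days after the eRATs are switched off, which pulls their rate ratios slightly towards 1

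*Protocol article*

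**What the plan says.** All references are to the protocol article.

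- **Data collection window:** "Outcome data for all practices will be obtained for the 2-year period from 1 June 2022 to 29 May 2024". No outcome has a window of its own. Two reasons are given for the lag behind trial time. The first is time for practices to get used to the software. The second is "to have a 2-month window following the end of the intervention window in order to allow cancers to be diagnosed".
- **Duration of intervention:** the intervention "will close for all intervention practices on 31 March 2024". Under Usual care, trial time for control practices ends on the same day.
- **Data analysis:** a single model form covers three kinds of count: "For rate outcomes (number of 2-week wait referrals, cancers and imaging investigations". The unit is a rate per 100 000 "registered patients per year by age–sex strata using mixed-effects Poisson regression models". The treatment term is one arm effect: "These models will include trial arm as a predictor and will adjust for the age and sex of the strata". No arm-by-period term, arm-by-age term or lower age limit is stated.
- **Introduction:** "The software performs daily calculations of individual cancer risk in patients aged 40 and over".
- **Secondary outcomes:** the change in investigation rates is the means of estimating any change in the expected number of adverse events, since routine data do not record such events directly.

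**The concern.** The tail after closure is justified as time for diagnoses to arrive "in order to allow cancers to be diagnosed in patients seen towards the end of that window". A diagnosis lags the consultation that led to it, so the tail is right for stage at diagnosis and for numbers of cancers. A referral or an investigation sits much closer to the prompt. Under Intervention, ordering tests and referring are among the options open to the clinician on seeing the score. From 1 April 2024 no prompt appears in either arm, so referrals and investigations after that date are largely usual care in both arms. They still enter one averaged arm effect.

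The age range raises a similar but less certain question. No risk is calculated below age 40, yet the rate denominator is described only as registered patients by stratum. Adjusting for age and sex does not remove dilution, because a single arm coefficient is averaged over all strata, including any in which no prompt can fire.

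At stake are secondary outcomes that describe the mechanism of the intervention, its call on diagnostic services and, through investigations, its expected procedural harm. The effect is attenuation of the ratio and some loss of power. It is not imbalance between arms.

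**Working it through.** **1. The plan's own figures.** 1 June 2022 to 29 May 2024, inclusive, is 729 days, which agrees with the stated two years to within two days. 1 April to 29 May 2024 is 59 days, which agrees with the stated two months. Exposed days: 729 − 59 = 670.

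**2. Unexposed share of time.** f = 59/729 = 0.081.

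**3. Dilution by time.** Assume events are spread evenly over the window and the intervention has no effect after closure. Then

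observed RR = 1 + (1 − f)(RR − 1).

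- RR 1.10: 1 + 0.919 × 0.10 = 1.092
- RR 1.20: 1 + 0.919 × 0.20 = 1.184

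The loss is 8.1% of the excess. It is an upper bound, because some April–May 2024 events will follow prompts given in March.

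**4. Does a shorter window cost more than it gains?** No power is stated for these outcomes, so take as an illustration 90% power for RR 1.20 with all 729 days exposed.

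- *Full window, diluted:* log(1.184)/log(1.20) = 0.926 of the signal is kept. Power = Φ(0.926 × (1.960 + 1.282) − 1.960), about 85%.
- *Window to 31 March:* the ratio is undiluted, but there are fewer events. In the least favourable case all the variance is Poisson counting error. The standard error then rises by √(729/670) = 1.043, so the signal-to-noise ratio is 1/1.043 = 0.959 of its full value. Power = Φ(0.959 × 3.242 − 1.960), about 87%.

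With no carry-over, the shorter window is no worse even in that case. The more the variance lies between practices, the closer it comes to 90%.

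**5. Dilution by age.** Let y be the share of control-arm events in patients under 40. The article does not give it, so 10% to 30% is assumed for illustration. With the time window already corrected and no effect under 40,

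observed RR = 1 + (1 − y)(RR − 1).

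| y (assumed) | RR 1.10 becomes | RR 1.20 becomes |
|---|---|---|
| 0% | 1.10 | 1.20 |
| 10% | 1.09 | 1.18 |
| 20% | 1.08 | 1.16 |
| 30% | 1.07 | 1.14 |

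With the uncorrected window as well, the factor is 0.919 × (1 − y), so the share of the excess lost is 17%, 26% or 36% for y = 10%, 20% or 30%.

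**6. Does dilution by age hide extra tests?** Take 100 control events, 40 of them under 40, and RR 1.10 in the other 60. The excess is 0.10 × 60 = 6. The all-age ratio is 106/100 = 1.06, and 0.06 × 100 is again 6. The ratio shrinks; the excess number does not.

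**The case against.** **The time part is small and assumes no carry-over.** A prompt may lead first to a review in primary care or to a test, with referral or imaging some weeks later, so a cut on 31 March drops some events that the intervention caused. This is fair as to size, and it is why 8.1% is a ceiling. It does not justify the tail. Data collection starts two months after the intervention opens, so events in June 2022 already include carry-over from April and May prompts. June 2022 to March 2024 is therefore exposed time throughout, apart from practices with delayed installation, which affect either choice of window alike.

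**The age part rests on silence.** The article does not say which age strata enter the rate models. The five-year groups it mentions are case-mix covariates. The full protocol or the SAP may set a lower limit. This stands, so it should not be stated as fact that under-40s are counted. The main 2-week-wait analyses are also confined to pathways relevant to the six eRAT cancers, where the under-40 share may be small.

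**Broad counting is partly intended.** The plan names a spillover effect beyond the eRAT cancers and allows for a practice-level one. All-pathway and all-age counts serve that question. This too stands. It also means that under-40s cannot be assumed unaffected and used as a negative control.

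**Harm and workload.** A reader might infer that including under-40s understates added investigations and so makes the tool look safer. Step 6 shows otherwise: all-age rates give the excess number of tests undistorted. For the time part, the total excess within the window is also unchanged; only the annualised excess falls, by at most 8.1%.

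**Conclusion.** The mismatch in time is explicit in the document. One window is fixed for all outcomes, the intervention closes 59 days before that window does, and the reason given for the gap applies to diagnoses only. For 2-week-wait referral and investigation rates it costs at most 8.1% of the excess (1.10 to about 1.092, 1.20 to about 1.184), assuming even event rates and no carry-over. This is a modest attenuation of secondary outcomes, in the same calendar period for both arms, and it is almost free to remove.

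The age point is a recommendation about reporting, conditional on the strata not already starting at 40. Its gain is in the size of the ratio and in power, and the amount depends on an event share that the document does not give.

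A reader might go further and want the primary stage analysis limited to patients aged 40 and over. Nothing in the document shows how much that would matter, and the point made here does not extend to it. The primary analysis set should stay as it is.

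**What to change.** 1. For 2-week-wait referral and investigation rates, make 1 June 2022 to 31 March 2024 the main window, with person-time to match, and report the full window to 29 May 2024 as a sensitivity analysis.
2. Keep the lagged window for stage at diagnosis and for numbers of cancers.
3. For the conversion rate, take referrals made by 31 March 2024 and let diagnoses up to 29 May 2024 count. This keeps the referral and diagnosis windows consistent.
4. Unless the strata already start at 40, report eRAT-pathway referral and investigation rate ratios at age 40 and over alongside the all-age rates. Use the all-age rates for spillover and for the excess number of tests.
5. Leave the primary stage analysis set unchanged.

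The cost is a few lines of analysis-plan wording and a date and age filter on data already planned. The downside is about 22 instead of 24 months of referral and investigation data (670 of 729 days), and the loss of some late events that follow March prompts. The sensitivity analysis will show how much these matter.

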#### Secondary outcomes

A range of secondary outcomes will be examined:

The binary stage at diagnosis of a further six cancers without eRATs will be identified from NCRAS, and compared between intervention and control practices. This is to investigate the possibility of a ‘spillover’ effect whereby eRATs are associated with increased diagnostic activity beyond the eRAT cancers.The practice’s number of patients diagnosed with the six eRAT cancers combined, and the total number of cancer cases, from NCRAS.The number of patients investigated or referred under the 2-week wait system for the six eRAT cancers combined, and in total, from Cancer Waiting Times data.Route to diagnosis from the Routes to Diagnosis Dataset,^18^ which uses Hospital Episode Statistics data. This will be categorised into four possible routes: emergency attendance, 2-week wait referral, GP referral and ‘other’. We will collect this information for each of the six eRAT cancers, and for the six comparator non-eRAT cancers.The 2-week wait performance measures, from Cancer Waiting Times data, for the six eRAT cancers combined, and for all cancer referrals:Whether a patient on a 2-week wait pathway received a diagnosis of cancer. When aggregated, for example at the practice level, and expressed as the proportion of patients who received a cancer diagnosis, this is known as the conversion rate.The duration between 2-week wait referral and diagnosis of cancer in days.Whether patients referred on a 2-week wait referral and who received a cancer diagnosis were diagnosed within 28 days, the Faster Diagnosis Standard (introduced in 2022).Detection rate—the proportion of a practice’s cancers which are identified via the 2-week wait pathway.Survival measures (from date of diagnosis): 30-day; 1-year (identified from NCRAS). 5-year survival will also be reported, but the main trial will report at 30 days and 1 year, with 5-year data being a subsidiary report. These outcomes will use all-cause mortality data from the Office for National Statistics.Adverse events (using data from the Diagnostic Imaging Dataset): these are expected to be few, and largely related to complications from hospital investigation, such as colonoscopy. There is no mechanism for adverse events to be collected using routine data. We will, however, estimate any change in the expected number of adverse events from imaging investigations (colonoscopies, sigmoidoscopies, upper gastro-intestinal endoscopies, chest X-ray examinations, abdominal ultrasound scans and abdominal CT scans) through investigating any change in the rate of these investigations in intervention practices relative to control practices (see data analysis section). Potential adverse psychological consequences of being labelled with ‘possible cancer’ will be further explored in the process evaluation.

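### The single lagged outcome window also governs investigation rates, the trial's only quantitative adverse-event proxy, so the first 61 days of the intervention window go uncounted and any switch-on surge would be missed

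*Protocol article*

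**What the plan says.** The Data collection window section sets one period for everything: "Outcome data for all practices will be obtained for the 2-year period from 1 June 2022 to 29 May 2024". It gives two reasons for lagging this behind the intervention window. The first is to "provide some time for practices to become accustomed to how the intervention functions prior to data collection". The second is to leave two months after the intervention ends, so that cancers in patients seen late can still be diagnosed.

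The Duration of intervention section gives the exposure dates. "The formal start of the intervention window will be 1 April 2022", with a note that some practices may install later, and the window "will close for all intervention practices on 31 March 2024". Recruitment "is expected to finish at the end of March 2022, including installation of the eRATs software".

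The section on the eRATs says that the prompt draws on coded symptoms and blood tests in the patient's "medical record from the previous 12 months, which are then assessed for the possibility of cancer". It appears when a registered user opens the record of a patient with a risk of 2% or more for at least one of the cancers.

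The Secondary outcomes section lists adverse events, states that routine data offer no way to collect them, and estimates the change in their expected number by "investigating any change in the rate of these investigations in intervention practices relative to control practices". The Data analysis section models these rates per 100 000 registered patients per year with mixed-effects Poisson regression. It gives them no window of their own.

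**The concern.** A run-in before counting suits an outcome such as stage at diagnosis: users are learning the tool, and a cancer takes time to be confirmed. It does not suit a harm measure. A patient sent for an endoscopy or a CT scan because of a prompt bears the risk of that test whether or not the GP is yet used to the software. In a practice live by 1 April 2022, that exposure starts two months before counting does.

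The look-back sharpens the point. At switch-on, anyone whose previous year of coded features already gives a risk of 2% or more can trigger a first prompt at the next opening of the record. The first weeks can therefore release a waiting pool as well as new cases. If that raises investigation rates, the rise falls partly or wholly in the uncounted period.

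The between-arm investigation rate is the only quantitative adverse-event measure in the article; the process evaluation takes up psychological consequences. The committee section explains that outcome data arrive only after practices have finished, so no interim look would reveal an early surge either.

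**Working it through.** **Inputs.** Intervention window 1 April 2022 to 31 March 2024 (Duration of intervention). Outcome window 1 June 2022 to 29 May 2024 (Data collection window). Rate scale (Data analysis). The documents give no investigation rates, so the size of any early excess has to be assumed.

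**Calendar, both ends inclusive.**
- Intervention window: 731 days. Outcome window: 729 days. This agrees with the plan's description of a 2-year window lagged by about 2 months.
- Uncounted at the start, 1 April to 31 May 2022: 30 + 31 = 61 days; 61/731 = 8.3% of the intervention window.
- Overlap: 731 − 61 = 670 days.
- Counted after the tool closes, 1 April to 29 May 2024: 30 + 29 = 59 days; 59/729 = 8.1% of the outcome window.

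**Effect of the start date on the rate.** Let the between-arm excess investigation rate be *e* over the 670 later live days and *k* × *e* over the first 61. The mean excess over the intervention window is *e* × (61*k* + 670)/731. The later rate *e* understates that mean by 1 − 731/(61*k* + 670).
- *k* = 1: 1 − 731/731 = 0. No bias in the rate.
- *k* = 2 (assumed): 1 − 731/792 = 7.7%.
- *k* = 3 (assumed): 1 − 731/853 = 14.3%.
- *k* = 0, the limit of no early excess at all: 731/670 = 1.091, so the later rate overstates the mean by 9.1%.

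The direction of the error therefore depends on whether *k* is above or below 1, and the documents do not settle that.

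**Effect of the end date.** If no prompt-driven excess remains after 31 March 2024, the excess averaged over the outcome window is 670/729 = 0.919 of the live rate, a dilution of 8.1%. Delayed investigations from late prompts would reduce this, so 8.1% is a ceiling under a constant later excess.

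**How fast a waiting pool would be released.** Prompts depend on records being opened. The share of an initial pool investigated before 1 June 2022, under assumed patterns for practices live on 1 April:
- Openings spread evenly over 12 months: 2/12 = 17%; with a one-month wait for the test, 1/12 = 8%.
- Exponential with mean 6 months: 1 − exp(−2/6) = 28%; with the wait, 1 − exp(−1/6) = 15%.
- Exponential with mean 2 months: 1 − exp(−2/2) = 63%; with the wait, 1 − exp(−1/2) = 39%.

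The pool is a fair inference from the look-back. How much of it falls before counting starts is open.

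**The case against.** The strongest reply is that a common window after familiarisation, the same in both arms, estimates a settled rate and keeps the randomised comparison intact. The article also expects adverse events to be few. That is a fair defence of the window for effectiveness and for a steady-state rate. It does not explain why exposure that has already begun should be left out of the harm measure.

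A reader might infer that investigation-related harm is likely to peak in April and May 2022. The documents do not support that. They speak of practices needing time to get used to the tool and of delayed installation in some. Prompts need a record to be opened, the clinician may choose review rather than a test, and waits carry some tests past 1 June. Patients in the pool already had coded symptoms or blood results, so some may have been investigated before. This part of the objection stands.

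A reader might also measure the loss as a share of excess investigations, 61*k*/(61*k* + 670): 8.3%, 15.4% and 21.5% for *k* = 1, 2 and 3. These are counts. The plan analyses rates, and on that scale the understatement is nil, 7.7% and 14.3%.

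Nor is 1 April a clean switch-on date. Installation was expected to finish by the end of March, so some practices may be live earlier and others later. It is tempting, too, to say that the service delivery modelling inherits the omission, but the article does not say that the modelling uses referral counts from this window.

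Finally, a full protocol or analysis plan might add a second window. The article does not leave the matter open, however: it states one window for outcome data from all practices, and no exception is given.

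**Conclusion.** The point holds as a cheap improvement to a secondary outcome. The only quantitative adverse-event proxy starts 61 days (8.3% of 731) after the intervention formally begins, for reasons that apply only to effectiveness. As planned, the trial could not tell whether investigations surged at switch-on.

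The size is conditional. With an early excess 2 or 3 times the later one (assumed), the later rate understates the excess over the intervention window by about 7.7% or 14.3%. With an equal early excess, the start date causes no bias in the rate; with a smaller one, the error runs the other way. Separately, up to 8.1% dilution can come from the 59 counted days after the tool closes. These figures treat all practices as live exactly on 1 April 2022; staggered installation would change them. The primary outcome is unaffected.

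**What to change.** Keep the lagged window for stage and the other cancer-diagnosis outcomes. In the Data collection window section, add that for investigation rates and 2-week wait referral counts:
- data will be obtained from 1 April 2022 in both arms;
- the rate over the whole period from 1 April 2022 to 29 May 2024 (790 days) will be reported, at least as a sensitivity analysis beside the planned window;
- April to May 2022 and the period after 31 March 2024 will each be shown separately.

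A calendar start common to both arms preserves the randomised comparison. The cost is two earlier months of routine data for these outcomes and a short addition to the text. The remaining weaknesses are some unexposed time from late-installing practices, and missed early exposure in any practice live before 1 April 2022; both should be acknowledged when the result is reported.
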